### Design

This study will be a randomised, assessor- and statistician-blinded, placebo-controlled trial. A total of 36 subjects with PDM who meet the guidelines of the Society of Obstetricians and Gynaecologists of Canada for the diagnosis of PDM will be recruited and randomly assigned to a shock wave group or a sham shock wave group at a 1:1 ratio. Table 1 lists the recruitment process, intervention methods and evaluation, and Fig. 1 depicts the experimental flow chart. The Standard Protocol Items: Recommendations for Interventional Trials (SPIRIT) 2013 checklist is attached as Additional file 1. This study commenced in January 2019 at the Zhongshan-Xuhui Hospital, Fudan University, Shanghai, China.

**Table 1 Tab1:** Study design schedule

Period	Screening	MRI scan	Treatment	MRI scan	Close-out
Menstrual cycle	0 month	1 month	1 month	1 month	1 month
Inclusion and exclusion criteria	√				
Informed consent	√				
Physical examination	√				
Medical history	√				
Comorbidities	√				
Pelvic MRI	√				
Allocation			√		
SF-MPQ		√		√	
CMSS		√		√	
SAS and SDS		√		√	
Patient compliance					√
Reasons for dropout or withdrawals					√
Adverse events					√
Safety evaluation					√

*CMSS* COX Menstrual Symptom Scale, *MRI* magnetic resonance imaging, *SAS* Zung Self-rating Anxiety Scale, *SDS* Self-rating Depression Scale, *SF-MPQ* Short form of the McGill Pain Questionnaire

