### Experimental ethics

The ethics-related aspects of this research were approved by the Institutional Review Board of the Institute of Clinical Trials. The experiment was reviewed and approved by the Ethical Committee of Zhongshan-Xuhui Hospital in January 2019 (approval no. 2018043). The study was registered in the Chinese Clinical Trial Registry in January 2019 (ChiCTR1900020678). This research conforms to the Helsinki Declaration.

Demographics data (height, weight, occupation, family history of dysmenorrhea, years of menstruating, age of onset of dysmenorrhea, menstrual cycle, number of days of menstruation, duration of dysmenorrhea per month (hours), aggravating/alleviating pain factors), questionnaire results, MRI results and signed consent forms will be gathered. All electronic data will be stored in encrypted computers and paper data will be locked in cabinets.

Any modification of the protocol will be documented at www.chictr.org.cn. The research team will disseminate the results of this study by publishing them in peer-reviewed journals.

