### Randomisation, concealment of allocation and blinding

Participants who meet the inclusion criteria will sign the informed consent form voluntarily and will be eligible for randomisation. They will be assigned randomly to the rESWT group or the sham rESWT group. The random sequence will be generated by a statistician using IBM® SPSS® statistics version 22.0 (IBM Institute, Inc., USA) who is not involved in the intervention or outcome evaluation.

The random number and group assignment will be sent immediately to the independent assessor by another research coordinator via an encrypted electronic file. As much as possible, evaluators will be prevented from communicating with the patients to avoid bias. This process will ensure that randomisation concealment will be competent and will be unaffected by the participants or practitioners.

It is not feasible for the therapist and the patient to be double blind because of the particularity of shock wave therapy. Before signing the informed consent form, patients will be told that they will receive shock wave treatment. Participants will not know their treatment allocation. The therapist will not be blinded, but will not assess the effectiveness of the treatment. Outcome assessors, data managers and statisticians will be blinded to treatment allocation. Prior to the start of the trial, all researchers will be trained to ensure the successful implementation of the blinding procedure.

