### Interventions

The time of interventions will be within the first 48 h of the menstrual period (Fig. 2). Trained and qualified practitioners from the Ministry of Health of the People’s Republic of China will perform real and sham rESWT therapy on the participants. Before the intervention, the myofascial trigger points in the abdominal muscles (Fig. 3) will be clinically located by the clinician, and ultrasound coupling gel will be applied on the lower abdominal skin surface (Fig. 2). In the real rESWT group, therapists will use radial shock wave devices based on previous experience to apply 5000 impulses of radial shock waves with a pressure of 1.5 bar at a rate of 10–14 impulses per second for each participant (STORZ MEDICAL AG, MASTERPULS® MP100, C15, diameter 15 mm, Switzerland) (Fig. 4 and Table 2) [9, 10]. Patients in the sham therapy control group will receive placebo intervention with the same sound but no energy input [17]. Moreover, any other treatment to improve menstrual pain will be restricted in both the real and sham rESWT groups during the trial.

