### Outcome measurements

#### Primary outcomes

##### SF-MPQ

The primary outcome will be the change in the short form of the McGill Pain Questionnaire (SF-MPQ) score (Table 1). The SF-MPQ is a scale composed of a pain rating index, a visual analogue scale and existing pain intensity to measure pain intensity. The pain rating index consists of 11 sensory and 4 emotional pain descriptors, all of which are rated from 0 to 3 points to indicate the different degrees of no, mild, medium, or severe pain, respectively. This index is a sensitive and reliable pain evaluation method widely used in the assessment of dysmenorrhoea [18].

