### Sample size calculation

The smallest significant differences in clinical treatment are considered to assess the effects of different treatments. SAS 9.4 software was used to design the two groups with better efficacy. The optimal value was defined as 15%. According to previous research results, the effectiveness proportion of shock wave treatment for primary dysmenorrhea is known to be 0.8 [9, 10]. The control group for this experiment was the sham shock wave treatment group. Through previous practice observation, we determined the effectiveness of the control group proportion to be 0.45. The estimated sample size was 30 individuals (15 in each group) to meet the 80% statistical value [21] and the 5% significance level. Considering a 20% drop-out rate, the sample size was finally determined to be 36 participants (18 per group).

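### The stated pre-consent information, that patients will receive shock wave treatment, is untrue as written for the half of the trial allocated to sham

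*Protocol article*

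**What the plan says.** The section on randomisation, concealment and blinding sets the order of events: "Participants who meet the inclusion criteria will sign the informed consent form voluntarily and will be eligible for randomisation". Later in that section it says what candidates hear beforehand: "Before signing the informed consent form, patients will be told that they will receive shock wave treatment". The next sentence is: "Participants will not know their treatment allocation".

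Under Design, participants are "randomly assigned to a shock wave group or a sham shock wave group at a 1:1 ratio". The sample size section gives 36 in total, 18 per group. The Interventions section describes the control: "Patients in the sham therapy control group will receive placebo intervention with the same sound but no energy input". It also restricts any other treatment for menstrual pain in both groups during the trial, and the termination criteria list the use of extra pain relievers during the treatment period.

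On ethics, the article reports committee approval and states: "This research conforms to the Helsinki Declaration".

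**The concern.** Whether one may be given an inert procedure is material to the decision to join. It matters more here because participants give up other relief during painful menstruation. A statement that shock wave treatment will be given, made to everyone and followed by random allocation of half of them to sham, does not describe what those patients are agreeing to. It also sits uneasily with the article's claim of conformity with the Helsinki Declaration.

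The article does not merely leave consent detail to a fuller document. It chose to state what patients are told, and that statement does not fit the design.

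There is a secondary statistical interest. The primary outcome is patient-rated ("The primary outcome will be the change in the short form of the McGill Pain Questionnaire (SF-MPQ) score"), and such scores can respond to expectation.

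**Working it through.** The point rests on wording. The only count needed is the number of people for whom the statement is untrue.

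1. **Who hears the statement.** It is made before the form is signed, and signing precedes eligibility for randomisation. Table 1 agrees: informed consent is marked at screening (month 0) and allocation in the treatment column (month 1). The statement therefore cannot be specific to an arm and goes to all 36.

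2. **For how many it is untrue.** Inputs: 36 participants (Sample size calculation) and a 1:1 ratio (Design). 36 × 1/2 = 18 allocated to sham, and 18/36 = 50%. This matches the article's own 18 per group.

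3. **What those 18 receive.** By the Interventions section and Table 2, a procedure without energy. The Discussion's looser description of a sham with almost no energy does not turn it into the treatment under test.

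4. **Whether the article says elsewhere that patients learn of the sham.** It does not. The statistical section says that participants receive instructions before taking part, without giving their content. One sentence among the limitations mentions participants together with the identification of shock wave types, but it is garbled and does not say what is disclosed before consent.

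5. **Effect on the comparison.** The sample size section assumes response proportions of 0.80 (real) and 0.45 (sham), a contrast of 0.80 − 0.45 = 0.35. If the common statement raised both by the same amount d, the contrast would be (0.80 + d) − (0.45 + d) = 0.35, unchanged. It would shrink only if expectation raised the sham response more than the active response. The document gives no figure for either rise.

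**The case against.** **The consent form is not shown, and the article is a condensed account.** The sentence reports one thing patients are told and does not claim to be the whole of it. This stands, and it limits the finding. A reader might infer that sham participants were never told they might receive no active treatment. The document does not say so; that would be an inference from silence.

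**The phrase might be a loose label for the session in either arm,** since the article also uses shock wave wording for the sham. This is possible but the less natural reading. The Design section sets a shock wave group against a sham shock wave group, and the sample size section sets shock wave treatment (0.80) against sham (0.45). Even if the label was meant loosely, a patient could not be expected to read it that way.

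**The sentence does not contradict the one after it.** This also stands. A reader might see a conflict with the statement that participants will not know their allocation, but if all are told the same thing, none learns her arm.

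**Expectation is equal in both arms.** This stands too. A reader might infer a biased comparison or a calculable loss of contrast. Neither is supported. A loss arises only by assuming a rise in the sham arm alone. The 0.45 comes from earlier practice observation, and what those patients were told is not given. The proportions are also not the primary outcome, which is a change in score.

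**Timing.** Recruitment began on 31 January 2019 and was expected to end around December 2019; the article appeared on 11 February 2020. On that timetable new wording may reach few or no new participants. This shifts the weight of the remedy towards reconciliation and notification but does not remove the need for it.

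**Conclusion.** The concern holds as a finding about a stated procedure. As written, the pre-consent statement is untrue for 18 of 36 participants (50%), who also face the restriction on other menstrual pain treatment. The count rests on the planned 36 and the 1:1 ratio, and on reading shock wave treatment as the active treatment, which is the article's own usage where it contrasts the arms.

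There are two possibilities. Either patients are in fact told of the sham, and the article misdescribes the procedure; or they are not, and consent is sought on an inaccurate statement. The document does not show which, and both require correction.

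For inference, raised expectation in both arms is at most a possible dilution of unknown size. It is not a between-arm bias.

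**What to change.** Replace the sentence with wording such as: before signing, patients are told that they will be assigned by chance, with equal probability, either to real shock wave therapy or to a sham procedure that sounds the same but delivers no energy, and that they will not know which during the trial.

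Check the consent form against this and align it. If it already discloses the sham, only the article's sentence needs correcting. If participants already enrolled were not told of the sham, take the question of notifying them to the ethics committee. Seven had been selected when the article was submitted, and more may have been since.

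The cost is one sentence, an ethics amendment if the form changes, and possibly notices to participants. The downside is that people who know a sham exists may try to guess their arm, and a few may decline. Participant blinding can be kept, since knowing that a sham exists is not the same as knowing one's own allocation.

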### Interventions

The time of interventions will be within the first 48 h of the menstrual period (Fig. 2). Trained and qualified practitioners from the Ministry of Health of the People’s Republic of China will perform real and sham rESWT therapy on the participants. Before the intervention, the myofascial trigger points in the abdominal muscles (Fig. 3) will be clinically located by the clinician, and ultrasound coupling gel will be applied on the lower abdominal skin surface (Fig. 2). In the real rESWT group, therapists will use radial shock wave devices based on previous experience to apply 5000 impulses of radial shock waves with a pressure of 1.5 bar at a rate of 10–14 impulses per second for each participant (STORZ MEDICAL AG, MASTERPULS® MP100, C15, diameter 15 mm, Switzerland) (Fig. 4 and Table 2) [9, 10]. Patients in the sham therapy control group will receive placebo intervention with the same sound but no energy input [17]. Moreover, any other treatment to improve menstrual pain will be restricted in both the real and sham rESWT groups during the trial.

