**Methods:**

This clinical research will be a randomised, blind, sham-controlled trial. Thirty-six patients with PDM will be randomly divided into the rESWT group (*n* = 18) and the sham rESWT group (*n* = 18). In the rESWT group, treatment will be applied once within 48 h of menstruation at six abdominal myofascial trigger points. The sham rESWT group will receive sham shockwave therapy on the same sites but without energy input. Other dysmenorrhoea-related treatments in both groups will be limited. The main indicators include the short form of the McGill Pain Questionnaire and the Cox Menstrual Symptom Scale. The secondary indicators include the Zung Self-rating Anxiety Scale and Self-rating Depression Scale and functional magnetic resonance imaging (fMRI) changes in brain regions. Results will be evaluated at the screening, at baseline, and before and after treatment, and adverse treatments will be examined. Inter- and intragroup analyses will be performed.

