**Fig. 4 Fig4:**
[figure not shown]
Description of the shockwave instrument. Above is the front view of the shockwave instrument (model: MASTERPULS MP100), and below is the side view of the treatment handle (model: R-SW handpiece)

**Table 2 Tab2:** Details of rESWT intervention

Item	Detail	Description
rESWT rationale	Type of shock wave	Pneumatic ballistic extracorporeal shock wave therapy
	Reasoning for treatment	The best treatment option was selected according to our previous study results and other clinical trials of rESWT for primary dysmenorrhoea
	Extent to which treatment varies	None
Details of rESWT	Number of treatment sites per subject	6
	Names of points used	Attachment point of rectus abdominis above the symphysis pubis (bilateral) (blue dot in Fig. 3)
		Intersection of the anterior superior iliac spine with the outer margin of the rectus abdominis (bilateral) (yellow dot in Fig. 3)
		The anterior superior iliac spine shifts inward by approximately 2 cm along the line (bilateral) (location of the red dot in Fig. 3)
	Shock wave intensity	1.5–2.0 bar
	Shock wave frequency	10–14 Hz
	Number of hits from each site	600 times
	Response sought	None
Treatment regimen	Number of treatment sessions	1 time
	Treatment time	Within 48 h of menstruating
Other components of treatment	Details of other interventions administered to the rESWT group	None
	Setting and context of the treatment	Hospital rehabilitation section, outpatient department
Background of practitioner	Profile of the therapist	Specialist in rehabilitation medicine or a resident of more than 1 year under the guidance of the specialist in rehabilitation medicine
Control or comparator	Rationale for the control or comparator in the context of the research question	As a placebo control, a non-energetic sham rESWT was used

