The limitations of this trial should be mentioned. A sham radial extracorporeal shock wave group will function as the control group in this study. Since no research is available on reliable treatment using sham shock waves, the principle of controlling with no energy output in previous clinical studies is applied. However, limitations occur with any type of sham shock wave. First, this is not a double-blind trial because those conducting the treatment cannot blindly assign treatment without knowing the type of treatment. To minimise the risk of bias, participants and evaluators will be carefully identified for their shock-wave types and trained in advance to apply a sham shock wave with the machine vibrating and pushing onto the handle with almost no energy. Second, a shock wave often shows a large nonspecific effect and produces physiological activity, which cannot be ignored during the experiment. Nonetheless, the neural mechanisms between different groups can be compared. Therefore, by using the MRI results, we can recognise rESWT-specific pathways related to pain amelioration, even if their effects are not significantly different. Third, a healthy group should not be used as a control group. Previous literature has shown differences in the brain networks of patients with PDM and healthy participants [27, 28]. Conversely, our study will focus on the functional brain changes that will be confirmed by extracorporeal shock wave rather than the PDM-specific features against healthy controls. Therefore, the comparison of the changes in brain networks between the rESWT and sham rESWT groups will be emphasised. Thus far, the randomised controlled trial has only been exploratory, but the prospects look promising. In the future, we expect to collect extensive samples with higher-quality randomised controlled trials.

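### The active shock wave dose is stated in two incompatible ways: 5000 impulses per participant in the text, against 6 × 600 = 3600 in the table that the text cites

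*Protocol article*

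**What the plan says.** In the protocol article, Methods, Interventions, therapists in the active arm are to "apply 5000 impulses of radial shock waves with a pressure of 1.5" bar, at 10–14 impulses per second, for each participant. That sentence closes with a reference to Fig. 4 and Table 2.

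Table 2 (details of the rESWT intervention) breaks the treatment down as follows:

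- Treatment sites per subject: 6, listed as three bilateral points.
- "Number of hits from each site": 600.
- Sessions: 1.
- Intensity: 1.5–2.0 bar.
- Frequency: 10–14 Hz.
- "Extent to which treatment varies": none.

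The abstract agrees on the number of sites and sessions: "treatment will be applied once within 48 h of menstruation at six abdominal myofascial trigger points".

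For the sham, the Interventions section specifies a "placebo intervention with the same sound but no energy input". The abstract and Table 2 also describe it as without energy. The limitations paragraph of the Discussion first appeals to the principle of no energy output, and then says that the sham will be applied "with the machine vibrating and pushing onto the handle with almost no energy".

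**The concern.** The text presents Table 2 as the detail behind its own figure, so the two should agree. They do not agree on the most basic element of dose, the number of impulses. On pressure, one gives a point value and the other a range.

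Two qualified therapists could each follow the protocol faithfully and treat participants differently. A reader of the eventual report could not say which dose had been tested, and another group could not reproduce it. The trial plans only 18 participants per arm, so there is little room to sort out mixed delivery afterwards. The Trial status section says that recruitment began on 31 January 2019 and that seven patients had been selected by the time of submission. The ambiguity may therefore already have affected delivery.

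**Working it through.** **Inputs**

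| Quantity | Value | Source |
|---|---|---|
| Impulses per participant | 5000 | Interventions |
| Sites | 6 | Table 2; abstract; three bilateral points in the Fig. 3 legend |
| Hits per site | 600 | Table 2 |
| Sessions | 1 | Table 2; abstract |
| Pressure, text | 1.5 bar | Interventions |
| Pressure, table | 1.5–2.0 bar | Table 2 |
| Rate | 10–14 per second | Interventions and Table 2, consistent |

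**Step 1: try to reproduce the text's 5000 from the table.**
Total = sites × hits per site × sessions = 6 × 600 × 1 = 3600. This does not reproduce 5000.

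**Step 2: size of the gap.**
- 5000 − 3600 = 1400 impulses.
- 5000 / 3600 = 1.39, so the text is 39% above the table.
- 1400 / 5000 = 0.28, so the table is 28% below the text.

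**Step 3: try other readings of the table.**
- Each bilateral pair counted as one site: 3 × 600 = 1800.
- Each of the six sites doubled for side: 12 × 600 = 7200.
- Solving for hits per site: 5000 / 6 = 833.3, not a whole number and not 600.
- Solving for sites: 5000 / 600 = 8.33, not a whole number and not 6.

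None of these gives 5000, and the article does not say that any impulses are delivered away from the six sites.

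**Step 4: pressure.**
2.0 / 1.5 = 1.33, so the top of the table's range is 33% above the text's value. The bottom of the range equals the text's value.

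**Step 5: is session length a useful measure of the conflict?**
- 5000 impulses: 5000 / 14 = 357 s (6.0 min) to 5000 / 10 = 500 s (8.3 min).
- 3600 impulses: 3600 / 14 = 257 s (4.3 min) to 3600 / 10 = 360 s (6.0 min).

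The two ranges meet at about 6.0 min. The permitted rate alone changes duration by a factor of 14 / 10 = 1.4, as much as the impulse discrepancy does. Session length therefore adds nothing to the finding.

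**Step 6: sham wording.**
The abstract, the Interventions section, Table 2 and the principle stated in the Discussion all say no energy. One later Discussion phrase says nearly none, with the machine vibrating.

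**The case against.** Several objections are fair, and most limit how far the point can be taken.

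*The pressure mismatch is smaller than the impulse mismatch.* This stands. A therapist using 1.5 bar satisfies both the text and the table. The table's entry that treatment does not vary sits under the rationale block and may only mean that the regimen is not individualised; the 10–14 Hz range sits in the same table without difficulty. Even so, a single value in one place and a range in the other need aligning.

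*A reader might infer that the whole contrast under test is undefined, or that the comparison is biased.* The documents do not support that. The comparison is active rESWT against a sham without energy. The device, applicator, sites, rate, timing and number of sessions carry no such conflict. The dose conflict does not enter the sample size calculation, which rests on response proportions of 0.8 and 0.45, or the planned tests. An inconsistent active dose blurs what was tested; it does not undo the randomisation.

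*A reader might infer that an unblinded therapist could adjust the dose to the patient's response.* Nothing in the article describes such adjustment. Table 2 answers none both for the response sought and for variation in treatment, there is one session, and the therapist does not assess effectiveness.

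*A reader might infer that the sham is not inert.* One loosely worded phrase in a limitations paragraph does not outweigh four statements of no energy. A handpiece that sounds and vibrates but transmits no shock wave could fit all of them. This is a matter of wording.

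*The article is a condensation, and delivered dose may be recorded on a case report form that is not shown.* That is possible, and the absence of such a form is not criticised here. But condensation explains omissions. It does not explain two stated figures that contradict each other.

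None of these objections reconciles 5000 with 3600.

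**Conclusion.** The point holds for the active dose. The impulse count is wrong as written in at least one place: 5000 in the text against 3600 implied by Table 2, a gap of 1400 impulses, with the text 39% higher. This rests only on figures printed in the article and on total impulses being sites × hits per site × sessions. The pressure mismatch (1.5 bar against 1.5–2.0 bar) is real but secondary. The sham phrase is a minor inconsistency.

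The consequence is that delivery may differ between therapists and that the result cannot be attributed to one stated dose. The effect of mixed delivery on precision cannot be quantified from the article, and none is claimed. The impulse conflict alone is enough to require correction, because it concerns the experimental treatment itself. This review takes no position on which impulse count, pressure or sham setting is right.

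**What to change.** 1. Reconcile the Interventions text and Table 2 to one impulse count, written so that the total equals sites × hits per site. If some impulses are meant to be delivered outside the six sites, say so and give the number.
2. State the pressure the same way in both places, and make the table's entry on variation consistent with it.
3. Report the impulses and pressure actually delivered to each participant, including anyone treated before the clarification, so that the dose tested can be described.
4. As a wording matter, align the limitations paragraph of the Discussion with the no-energy sham described in the abstract, the Interventions section and Table 2.

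The article says that protocol modifications will be documented on the trial registry, so the clarification belongs there too. The cost is a short textual correction and, if delivered dose is not already captured, one line on the case report form. Sample size, randomisation and analysis do not change.
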